## Abstract

**Background/Objectives:** In recent years, the advent of new technologies has fostered their application in neuro-psychomotor and language rehabilitation, particularly since the COVID-19 pandemic. Tele-rehabilitation has emerged as an innovative and timely solution, enabling personalized interventions monitored by clinicians. TABLET TOSCANA project aims to develop innovative tele-rehabilitation organizational models in children, adolescents and young adults with congenital and acquired developmental disabilities, using the Virtual Reality Rehabilitation System (VRRS) Home Kit and the MedicoAmico APP. **Methods:** The trial is designed according to the CONSORT statement guidelines. The project encompasses three phases: adapting the technologies for pediatric use, validating them through a wait-list study, and analyzing feasibility and effectiveness data to define new organizational models. A randomized wait-list-control study with 100 subjects aged 6 to 30 years will compare tele-rehabilitation versus prosecution of standard care. **Discussion:** Although literature highlights tele-rehabilitation benefits such as improved access, cost savings, and enhanced treatment adherence, practical implementation remains limited (i.e., the definition of standardized procedures). TABLET TOSCANA project seeks to address these gaps by focusing on multi-domain treatments for neurodevelopmental disabilities and emphasizing the integration of tele-rehabilitation into local health services. **Conclusion:** The project aims to improve the continuity and intensity of care through innovative models that integrate tele-rehabilitation into local health services. The results could inform healthcare policies and promote the development of innovative and collaborative models of care, paving the way for more effective and widespread tele-rehabilitation solutions and fostering collaborative networks among professionals.

## 1. Introduction

In the last few years, there has been a significant increase in the development and application of new technologies for functional rehabilitation in developmental disabilities [1,2]. This trend has been further accelerated by the COVID-19 pandemic [3], which led to the complete closure of both public and/or private rehabilitation services, known as lockdown, across Italy, including the region of Tuscany. Specifically, within Tuscany, a significant decrease was observed in non-urgent medical procedures for both diagnosis and treatment. This reduction encompassed rehabilitative interventions, such as physiotherapy, speech therapy, and neuropsychological therapy [4]. Among the various consequences of the COVID-19 pandemic, a significant negative indirect impact on the quality of life of children with neurodevelopmental disabilities and their families was observed, including COVID-19-related rehabilitation services closure [5]. A longitudinal Italian study conducted during this period investigated lockdown-related emotional and behavioral changes in the pediatric neuropsychiatric population, revealing the increase in psychiatric symptoms [6].

To deal with this emergency, following the recommendations of scientific societies within the field, including Italian Society of Child and Adolescent Neuropsychiatry (SINPIA), Italian Society of Physical and Rehabilitation Medicine (SIMFER) and Italian Society of Neurological Rehabilitation (SIRN), some healthcare facilities responded by initiating tele-rehabilitation treatments, even if on a limited scale [7], and telehealth in their clinical practice with encouraging results [8,9,10].

Tele-rehabilitation is designed by the American Telemedicine Association as the provision of rehabilitation services through Information and Communication Technologies (ICT) [11] and is conceived as a timely, intensive, and personalized intervention aimed to provide access to rehabilitation services monitoring by clinicians.

This innovative approach facilitates activities in an ecological and home-based environment, ensuring continuity of care both spatially, at a distance from the clinical center, and temporally, extending the care beyond the hospitalization period [12]. In addition, it offers substantial cost and healthcare time savings [13] for both families and the healthcare system, increasing frequency and adherence to therapy [14], as well as treatment dosage and intensity [15], while also maintaining high levels of patient’s satisfaction [14,16,17]. However, several barriers have been identified in studies, such as technical literacy, availability of technology, connectivity issues and access to a sufficiently fast internet connection [18,19]. Technical literacy, in particular, is often associated with age or socioeconomic status [20].

New technologies to be integrated into rehabilitation pathways are even more crucial in the pediatric population, considering the prolonged treatments of neurodevelopmental disabilities as life-long conditions and, consequently, the extended hospitalization periods. Tele-rehabilitation allows us to address these issues, providing continuous home-based rehabilitation, supporting in the meanwhile motivation, and leveraging high-intensity interventions as key training elements highlighted in the literature [3].

Tele-rehabilitation, indeed, according to recent feasibility studies [21,22,23], proved to be particularly suitable to support the treatment of children with neurodevelopmental disorders and their families in order to enable continuity of care by extending rehabilitation programs into home settings, fostering family involvement with the continuous monitoring of the clinical team. This was even more relevant during the critical period of the COVID-19 emergency, as the use of ICT proved indispensable for the uninterrupted care of patients and their families and, consequently, mitigate the adverse consequences of care disruptions on the short-, medium-, and long-term neuropsychological outcomes, stress levels, and overall quality of life for the entire family [24].

A recent systematic review [25] investigating key aspects of tele-rehabilitation protocols for children with neurodevelopmental or neurological disorders revealed a heterogeneous and evolving landscape regarding the technologies used, intervention protocols, treatment efficacy and parent role during tele-rehabilitation. Results underscored the necessity for further improvements, especially in developing comprehensive and multi-domain rehabilitation protocols, and encouraged a more active role of the caregiver during treatment. This emphasizes the importance of home-based and family-centered care, potentially leading to better clinical outcomes for children with neurological or neurodevelopmental disorders.

Among the ICT, virtual reality can provide realistic experiences offering enhanced feedback (auditory, visual and tactile) in a user-friendly enriched environment [26], promoting enhanced learning and recovery for patients [27]. Moreover, virtual reality technologies align with rehabilitation principles, emphasizing the importance of meaningful, specific, and repetitive tasks and gradually increasing task difficulty over time [28,29]. Studies have reported the effectiveness of virtual reality in adult rehabilitation [17,30,31] and, although in fewer numbers, in children with neurodevelopmental disorders [32,33], including in tele-rehabilitation settings [34,35,36]. In this context, among different virtual reality tools the Virtual Reality Rehabilitation System (VRRS) developed by Khymeia (Padua, Italy) represents a promising device for rehabilitation. This multi-domain and integrated ecosystem supports neurological, orthopedic, cognitive speech, cardiorespiratory, and postural rehabilitation settings, mainly in the adult population.

Within this framework, TABLET TOSCANA aims to develop innovative organizational models that foster the continuity of care through tele-rehabilitation for neuro-psychomotor and language functions using Khymeia technological devices in subjects with congenital and acquired developmental disabilities. Particularly, organizational dimensions, acceptability, the usability of proposed solutions, and the performance of the involved ICT, unrelated to the effectiveness of tele-rehabilitation, will be assessed as the primary objective of the study, differently from traditional literature. In addition, the secondary objective will be to evaluate the clinical effectiveness of the tele-rehabilitation intervention. We hypothesize that the TABLET TOSCANA project could establish a new organizational model to be implemented at the territorial level and integrated into routine clinical practice, improving the taking charge of the rehabilitation services for children with neurodevelopmental disabilities.

## 2. Materials and Methods

### 2.1. Study Design

The TABLET TOSCANA study will be carried out in 3 main phases (Figure 1) in order to implement new technological solutions for taking care and tele-rehabilitation, such as MedicoAmico PRO and Home Kit VRRS (Khymeia, Padua, Italy). The involved clinical centers include the Department of Developmental Neuroscience IRCCS Fondazione Stella Maris and the Azienda USL Nord-Ovest, dealing with subjects with congenital and acquired disorders.

#### 2.1.1. Phase I

The initial phase will involve the adaptation of both the MedicoAmico APP and VRRS Home Kit to the pediatric population’s specific needs since such tele-rehabilitation devices were originally designed for adults. The multidisciplinary clinical team, in collaboration with Khymeia bioengineers, in relation to their expertise, will meticulously analyze and implement the library of motor, cognitive and language exercises currently available in both systems to enhance their usability for the developmental age. Detailed descriptions of these technologies will be provided in the “Intervention” section below. In addition, during this phase, new organizational models for motor, cognitive and/or language tele-rehabilitation pathways of children and adolescents with congenital or acquired developmental disorders will be hypothesized, as detailed in Figure 2.

#### 2.1.2. Phase II

During this phase, the validation of the implemented technologies will be conducted through a wait-list study (Figure 3) with two parallel arms. One hundred subjects (comprising 80 children and 20 young adults) will be recruited from the aforementioned clinical centers. The wait-list design study will ensure that all enrolled patients will be eligible for the experimental treatment, thus avoiding issues related to equipoise.

After the identification of eligible subjects according to inclusion and exclusion criteria (described below), participants will be stratified according to several criteria, including (i) diagnosis (congenital or acquired developmental disorder group), (ii) gross motor function classification system (GMFCS) level (GMFCS I–II/GMFCS III–IV), (iii) age group (6–10/11–15/16–20/21–30), (iv) and technology utilized (APP vs. Home Kit). Then, participants will be randomly assigned to the experimental group (EG)—receiving a 3-month tele-rehabilitation immediately—or the wait-list group (WG)—continuing traditional rehabilitation care for the same duration. All subjects will be evaluated before (T0) and after (T1) the 3-month intervention period (tele-rehabilitation or traditional rehabilitation), using standardized clinical tests. Moreover, participants enrolled in the WG will be re-evaluated at the end of the 3 months of tele-rehabilitation training (T1 plus). Finally, at the end of tele-rehabilitation training, ad-hoc questionnaires will be administered to the main stakeholders to assess the systems’ usability and acceptability. The program of enrolment, interventions and assessments designed according to SPIRIT guidelines are shown in Figure 4.

#### 2.1.3. Phase III

The third and final phase will involve the analysis of usability and acceptability data, considering the feasibility measures acquired. Moreover, efficacy data acquired from pre–post-intervention cognitive, motor, and language assessments will be considered. Furthermore, the research group will perform interviews with patients and parents to collect information regarding unmet needs in relation to the patient’s pathway. The healthcare professionals will be involved in a Focus Group to analyze the strengths and weaknesses of organizational models with and without technology. The interviews with patients and caregivers will be one-on-one and face-to-face. The interviews will be performed online. The interview will follow a semi-structured questionnaire that the research group will develop for the project. The Focus Group is a qualitative methodology based on discussion among participants managed by a moderator. The Focus Group with healthcare professionals will conduct in presence in groups of up to 12 participants. It is planned to carry out two Focus Groups, one with professionals from the Azienda USL Toscana Nord Ovest and one with professionals from the IRCCS Stella Maris. The obtained results will allow the definition of innovative organizational models, including tele-assistance and tele-rehabilitation pathways, to be validated and thus integrated into the planning of the Regional Health Service (SSR).

### 2.2. Ethical Approval

The present study was approved by the Paediatric Ethics Section of the Tuscany Regional Ethics Committee (Italy), with study opinion registration number 303/2021, 30 November 2021. Written consent will be obtained from participants and/or their caregivers of eligible subjects after being verbally informed about the trial by the Principal Investigator or the research collaborators mentioned in the ethical committee-approved protocol. A child-friendly format will be provided for participants aged 7–14, too. Any pertinent modifications to the protocol will be promptly communicated to the aforementioned Ethical Committee for review and approval.

An appropriate electronic access system, secured with passwords, will be used for data collection and management. Conforming to the current privacy standards, each patient will be assigned a unique alphanumeric code. The record linking each child’s name to the assigned code will be securely maintained by the Principal Investigator.

In addition, the study has been registered in the Clinical Trial Protocol Registry and Results System (ClinicalTrials.gov, accessed on 22 January 2024, code: NCT06219447).

### 2.3. Sample Size

Based on the annual count of children referred to the recruiting centers for clinical management and rehabilitation, a final sample of 100 subjects is deemed sufficient for conducting a *t*-test to analyze differences in primary endpoints between groups, assuming an effect size (d) of at least 0.4, a significance level (α) of 0.05, and a power (1-β) of 0.8.

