### 2.6. Outcome Measures

#### 2.6.1. Primary Outcome Measures

The acceptability and usability of ICT technologies in pediatric populations will also be assessed through the following Key Performance Indicators (KPIs), summarized in Table S1.

Service and technology KPIs:Study adherence: rate of acceptance of the participation in the study calculated as the number of eligible participants that agree to join the project;Adherence to training: total number of training sessions completed on the total number of sessions scheduled by the clinicians;Number of dropouts: number of participants that will not complete all of the study procedures;Number of sessions completed in the target time: total number of training sessions completed in the timeframe set by clinicians;Hardware and software technical problems: number of issues and malfunctioning experiments during the training sessions;Ad hoc feasibility questionnaires: according to the standard definitions of usability [49,50,51] and acceptability [52], specific items ranked on a five-point Likert scale (1 most negative, 5 most positive) will be defined. The aim will be to investigate four feasibility domains: (i) exercise customization, (ii) adaptability of home training, (iii) required effort and (iv) systems suitability. An introductory section will include both open and multiple-choice questions to collect information about the patient, the experimenter who fills out the questionnaire, and the devices and peripherals used. Three questionnaire versions will be available for different stakeholders (participants, parents, clinicians). The children’s format will be structured to be easy to understand for even the youngest participant and facial expressions shown through emoticons will help the children to assign the Likert-scale rank. Questionnaires will, therefore, be filled out at the end of the training by clinicians who administered the session, parents and participants over 6 years old and with cognitive and neuropsychological functioning, allowing full question comprehension and adequate cooperation;Medical Equipment Utilization: for each involved technology: the average time of utilization per session; the related consumables (if any)—the related power consumption;Set-up time: the time necessary for setting up the involved technologies;Training time/learning curve (for patients).

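### With 50 per arm, 100 participants give about 51% power at d = 0.4 instead of the stated 80%, and recruiting exactly that number leaves no margin for losses before T1

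*Protocol article*

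**What the plan says.** Section 2.3 (Sample Size) states that "a final sample of 100 subjects is deemed sufficient" for a t-test "to analyze differences in primary endpoints between groups". The inputs are given as "assuming an effect size (d) of at least 0.4", "a significance level (α) of 0.05" and "a power (1-β) of 0.8". Whether the test is one-sided or two-sided is not stated.

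The number enrolled is the same. Section 2.1.2 (Phase II) says: "One hundred subjects (comprising 80 children and 20 young adults) will be recruited from the aforementioned clinical centers". The Abstract also describes "A randomized wait-list-control study with 100 subjects aged 6 to 30 years". Section 2.4 sets 1:1 allocation, which makes 50 per arm.

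Section 2.1.2 assesses both arms at T0 and, three months later, at T1. Wait-list participants then receive three months of tele-rehabilitation and are assessed again at T1 plus. Section 2.6.1 lists among the primary indicators: "Number of dropouts: number of participants that will not complete all of the study procedures". The article gives no expected dropout rate.

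**The concern.** Section 2.3 makes a checkable claim: this total, this test, this effect, this alpha, this power. It does not look consistent with two arms of 50, because a standardised difference of 0.4 normally needs about twice that number for 80% power.

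The same figure also serves both as the final sample and as the number recruited. The two coincide only if nobody is lost before the between-arm assessment, so the stated power has no margin.

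What is at stake is how the randomised comparison will be read. If readers believe that the trial had 80% power for d = 0.4, they will take a non-significant result as fair evidence against an effect of that size. At about 51% power, a true effect of 0.4 would be missed roughly half the time.

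**Working it through.** **Inputs**
- Total 100, d = 0.4, alpha 0.05, power 0.8, between-group t-test: section 2.3.
- 100 recruited: section 2.1.2 and the Abstract.
- 1:1 allocation: section 2.4. This gives n = 50 per arm.
- Sidedness: not stated, so both were tried.
- Loss before T1: not stated. 10% and 20% are assumptions, shown as a range and split equally between arms.
- The comparison is taken to be experimental against wait-list at T1, the last assessment before the wait-list arm starts tele-rehabilitation.

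**Step 1: try to reproduce the stated 100.** By the normal approximation, n per arm = 2(z_alpha + z_beta)² / d².
- Two-sided: 2(1.960 + 0.842)² / 0.16 = 98.1, so 99 per arm and 198 in total. The exact noncentral t gives 99.08, so 100 per arm and 200 in total.
- One-sided: 2(1.645 + 0.842)² / 0.16 = 77.3, so 78 per arm and 156 in total. The exact t gives 77.97, also 78 per arm.
- A paired t-test, which is not what section 2.3 describes, needs 52 participants two-sided or 41 one-sided.

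None of these gives a total of 100.

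**Step 2: power at 50 per arm with full retention.** The noncentrality is d × √(n/2) = 0.4 × √25 = 2.0.
- Two-sided: Φ(2.0 − 1.960) = 51.6% by the normal approximation; exact t 50.8%.
- One-sided: Φ(2.0 − 1.645) = 63.9%; exact t 63.4%.

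Against 80%, the shortfall is 80 − 50.8 = 29.2 points two-sided, or 80 − 63.4 = 16.6 points one-sided.

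**Step 3: effect detectable with 80% power at 50 per arm.** By the normal approximation, d = (1.960 + 0.842) × √(2/50) = 0.56. The exact t gives 0.566, or 0.57. One-sided, the exact value is 0.50.

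**Step 4: loss before T1 (exact t).**

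| Assumed loss | Analysed per arm | Two-sided power at d = 0.4 | One-sided power at d = 0.4 | Detectable d (80% power, two-sided) |
|---|---|---|---|---|
| 0% | 50 | 50.8% | 63.4% | 0.57 |
| 10% | 45 | 46.7% | 59.4% | 0.60 |
| 20% | 40 | 42.4% | 55.1% | 0.63 |

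Two-sided, attrition costs a further 50.8 − 46.7 = 4.1 points at 10% and 50.8 − 42.4 = 8.4 points at 20%. The gap of about 29 points exists before any loss.

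**Step 5: which losses count.** A wait-list participant who leaves after T1 has already contributed to the T0–T1 comparison, so the table covers only losses before T1. Later wait-list losses affect the end-of-training questionnaire and part of the training indicators. Only part, because completed sessions, technical problems and time of use accumulate while training is under way.

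**The case against.** The strongest reply is that a missing dropout allowance is an omission, and a journal article may leave it to the full protocol or analysis plan. That is right as far as it goes: silence on attrition would not be a finding by itself. It does not cover the power statement, which the article makes itself and which does not hold at any level of retention.

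A second reply is that section 2.3 only deems 100 sufficient, and that final may simply mean the enrolment figure settled on after considering annual referrals. Both readings are possible. Neither helps, because the sentence still attaches d = 0.4 and power 0.8 to that number, and 50 per arm does not deliver them.

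Three stronger readings are tempting but not supported:
- A reader might infer that the stated power is sound and is lost only when participants leave. The arithmetic shows otherwise: attrition adds to a shortfall that is already there.
- A reader might infer that the plan forecasts losses because it counts dropouts as a primary indicator. Counting dropouts measures feasibility; it predicts no rate. The definition also covers anyone who misses any study procedure, so it includes wait-list participants who leave after T1 and still count in the between-arm comparison.
- A reader might infer that the per-arm requirement, 99.08 rounded up to 100, was mistaken for the total. The match is striking, but the article does not say how 100 was obtained.

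**Conclusion.** The point holds. On the article's own inputs, 100 participants split 1:1 give about 51% power two-sided, or 63% one-sided, for d = 0.4 with nobody lost. The trial can detect d = 0.57 two-sided, or 0.50 one-sided, with 80% power.

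Having no margin between the number recruited and the number called final makes this moderately worse: about 47% and 42% two-sided at assumed losses of 10% and 20%, with detectable effects of 0.60 and 0.63. Those two rates are illustrations, since the article supplies none.

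The result rests on an unadjusted two-sample t-test, equal arms, equal loss in both arms and a comparison at T1. The conclusion that 80% is not reached does not depend on sidedness or on any dropout assumption.

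**What to change.** Keep recruitment at 100 and reword section 2.3 so that it:
- says that 100 is the number recruited, 50 per arm;
- states whether the test is one-sided or two-sided;
- states an assumed loss by T1 and the resulting number analysed (for example, 90 at 10% or 80 at 20%);
- replaces the 80% power claim with either the power at d = 0.4 or the effect detectable with 80% power, both for 50 per arm and for the number expected at T1.

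Adding a dropout allowance to 100 would not repair the statement. Recruiting 112 (100/0.9, rounded up) or 125 (100/0.8) would only keep 100 analysed, where two-sided power is still about 51%.

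The cost is a reworded paragraph. No extra patients or assessments are needed. The only downside is a less favourable stated figure.

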As mentioned above, after the enrolment, participants will be stratified according to several criteria, including (i) diagnosis (congenital or acquired developmental disorder group), (ii) GMFCS level (GMFCS I-II/GMFCS III–IV), (iii) age (6–10/11–15/16–20/21–30), (iv) and technology utilized (APP vs. Home Kit). Randomization, sequence generation and preparation of group allocation materials will be carried out by an independent researcher who will not be involved in the trial. Using a computer-generated set of random numbers, they will be then allocated to experimental or control groups. Participants, parents, and clinical staff will be aware of the allocation group. Pairs will be randomly divided into two groups with a 1:1 experimental/SC (wait-list) ratio. Participants assigned to the experimental group will begin treatment with technology immediately for a 3-month period, while those in the SC group will continue with their usual care.

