### 2.7. Statistical Analyses

Descriptive statistics (means, standard deviation, frequencies) will be investigated, analyzing potential baseline differences between groups explored and computing the p values. The normal distribution of the sample will be investigated through the Shapiro–Wilk test. Subsequently, a comprehensive analysis, both qualitatively and quantitatively, will be conducted on the questionnaire data gathered from various stakeholders, aiming to assess the usability and acceptability of the devices used. Statistical analysis, such as ANOVA or regression, will be carried out to determine differences based on age, diagnosis, functional profile (cognitive and motor outcomes), and devices used during tele-rehabilitation. Furthermore, inferential analyses will be carried out to assess pre–post-treatment differences, gain efficacy data, and also consider the different devices used during tele-rehabilitation pathways. Finally, flowchart diagrams will be created to illustrate the different organizational models identified. Statistical significance will be considered at p<.05. Statistical Package for Social Sciences (SPSS) (IBM Statistic) will be adopted for carrying out the statistical analyses.

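### The only test named for the experimental versus wait-list comparison is an unadjusted t-test, although allocation is stratified on four factors and the clinical tests have a baseline score

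*Protocol article*

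**What the plan says.** Section 2.3 bases the size of the trial on "conducting a *t*-test to analyze differences in primary endpoints between groups". The inputs it gives are 100 subjects in total, a standardised difference of 0.4 or more, a 5% level and 80% power. It mentions no covariate.

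Section 2.4 (and likewise 2.1.2) says that "after the enrolment, participants will be stratified according to several criteria". The factors are diagnosis (2 levels), GMFCS group (2), age band (4) and technology (2), with 1:1 allocation.

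On measurement, section 2.1.2 states: "All subjects will be evaluated before (T0) and after (T1) the 3-month intervention period (tele-rehabilitation or traditional rehabilitation), using standardized clinical tests". These standardised tests are the secondary outcomes of section 2.6.2. The primary outcomes in 2.6.1 are service, technology and operational KPIs, and the usability and acceptability questionnaires are given only once tele-rehabilitation has ended.

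Section 2.7 describes three uses of the data that bear on this point:
- At baseline, it plans "analyzing potential baseline differences between groups explored and computing the p values".
- After the sentence on questionnaire data, it plans ANOVA or regression for differences by age, diagnosis, functional profile and device. Study arm is not in that list.
- It plans inferential analyses of pre–post differences, with neither the method nor the covariates named.

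**The concern.** Stratifying allocation on prognostic factors makes the arms more alike than simple randomisation would. A plain two-sample t-test does not recognise this. The variance that the factors explain stays in the error term, so the standard error overstates the true sampling variation of the arm difference. Confidence intervals are then too wide and the real type I error falls below the nominal 5%. Power that the design has already paid for is not used.

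For the clinical tests, the T0 score is a second source of precision that every subject is due to provide, and the article does not say that the arm comparison will use it. The only between-group use of baseline data that it states is significance testing of baseline differences. Under proper randomisation such p-values test a null hypothesis known to be true, and they invite covariates to be chosen after the data have been seen.

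At stake is precision in a trial that has little to spare, not false-positive findings.

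**Working it through.** **Inputs from the protocol article.** Total 100 subjects, d = 0.4, alpha 0.05, power 0.8 (section 2.3). Allocation 1:1 (section 2.4), hence 50 per arm. Sidedness is not stated; two-sided is used below.

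**Assumed inputs.** The article gives neither the share of outcome variance explained by the stratification factors (R²) nor the T0–T1 correlation (rho). Ranges are shown for both. The degrees of freedom spent on covariates are ignored.

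**1. The plan's own figure.** A two-sided two-sample t-test at d = 0.4 and 80% power needs about 99 per arm, 198 in total (78 per arm, 156 in total, if one-sided). The stated 100 does not reproduce. With 50 per arm, power from the noncentral t is 50.8% two-sided (63% one-sided).

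**2. Adjusting for the stratification factors only.** The residual SD falls by the factor √(1 − R²), so the effective effect size is 0.4/√(1 − R²). If the factors are balanced by design, the real type I error of the unadjusted test is 2·[1 − Φ(1.96/√(1 − R²))].

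| R² (assumed) | Effective d | Adjusted power, 50 per arm | Real type I error of unadjusted test |
|---|---|---|---|
| 0 | 0.400 | 50.8% | 5.0% |
| 0.10 | 0.422 | 55.1% | 3.9% |
| 0.20 | 0.447 | 60.0% | 2.8% |
| 0.30 | 0.478 | 65.8% | 1.9% |

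A simulation of 8,000 trials, with balanced blocks of four within strata, gave a type I error of 3.9% at R² = 0.10 and 2.0% at R² = 0.30. This agrees with the formula.

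**3. Adjusting for T0 (clinical tests only).** The effective effect size is 0.4/√(1 − rho²). With 50 per arm, rho = 0.3, 0.5 and 0.7 give d = 0.419, 0.462 and 0.560, and power 54.6%, 62.8% and 79.2%. These figures apply d = 0.4, which section 2.3 sets for the primary endpoints, to secondary outcomes, so they are illustrative.

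**4. Fewer subjects per test.** Section 2.6.2 selects tests to suit each patient's profile, so 50 per arm on any one test is unlikely. With an assumed 20 per arm and rho = 0.5, power is 23.4% unadjusted and 29.6% with ANCOVA. The gain is about 6 points, against 12 points (62.8 − 50.8) at 50 per arm.

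**5. What adjustment would need to reach 80%.** Under the normal approximation, the required R² is 1 − (0.4² × 50/2)/(1.96 + 0.8416)² = 1 − 4.00/7.85 = 0.49. This corresponds to a correlation of about 0.70.

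**6. Number of strata.** 2 × 2 × 4 × 2 = 32 cells, and 100/32 ≈ 3.1 subjects per cell. Adjustment therefore has to use main effects, not crossed cells.

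**The case against.** The strongest reply is that section 2.3 gives a sample-size basis. An unadjusted t-test is a common simplification for sizing, covariate lists usually belong in an analysis plan that is not shown, and the article nowhere says that the comparison will be unadjusted. Section 2.7 also names ANOVA or regression with variables close to the stratification factors, and any pre–post analysis must use T0 in some form. This stands in part: the article is silent on covariates and does not rule them out. The t-test is nevertheless the one arm comparison it states, the ANOVA or regression is not described as a comparison of arms, and the baseline p-values are positively planned.

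A reader might infer that the named t-test discards the T0 score. The article does not support that. The t-test is tied to the primary endpoints, and those that come from training or from the end-of-training questionnaires have no T0 value. The clinical tests do have one, but no test is named for them. A reader might also infer that baseline p-values are meant to replace adjustment; section 2.7 does not say so.

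Three further limits stand:
- Many primary KPIs arise only from tele-rehabilitation, which the wait-list arm has not had at T1, and others are facility-level. Adjustment can help only those that exist per participant in both arms.
- Some KPIs, such as dropout, are binary, so a linear model would not fit all of them.
- Age may explain less variance where age-normed scores are used, and section 2.6.2 refers to tests with normative data.

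**Conclusion.** The point holds as an improvement to a stated method. The only named arm comparison makes no use of the four stratification factors, and the analysis of the clinical tests is not tied to an arm comparison that uses T0.

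If the factors are balanced and explain 10% to 30% of the variance, leaving them out costs about 4 to 15 points of power at 50 per arm (55.1 − 50.8 and 65.8 − 50.8) and makes a nominal 5% test run at about 3.9% to 1.9%. These sizes rest on assumed R², on d = 0.4 and on 50 per arm. In absolute terms the gain is smaller for tests that few subjects take. The error is conservative: the t-test does not produce excess false positives.

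It would go too far to say that adjustment rescues the sample size. The gap between 51% and the stated 80% power is a separate and larger fault in section 2.3, and covariates close it only if they explain about half the variance.

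**What to change.** Name the between-arm analyses in section 2.7 and bring section 2.3 into line with them:

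- **Clinical outcomes:** ANCOVA of the T1 score on arm, adjusted for the T0 score and for diagnosis, GMFCS group, age and technology as main effects. Where few subjects take a test, cut the covariates to T0 and age by a rule set in advance.
- **Participant-level primary KPIs that exist in both arms:** a regression suited to the outcome type (linear if continuous, logistic if binary) with arm and the stratification factors, and no T0 term. List which KPIs qualify.
- **Baseline:** describe by arm, without p-values.
- **Covariates:** state that they are fixed before the data are seen.

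The change is wording only. Every covariate is already collected for stratification or at T0, and SPSS, the package named in section 2.7, fits these models. The full model spends about 5 to 7 degrees of freedom. The sample-size statement needs its own correction, because this change does not make 100 subjects sufficient for 80% power at d = 0.4 unless R² is near 0.5.
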